**Nature and extent of the burden and risks associated with participation, benefit and group relatedness**

For all participants, the selection assessment will take approximately 60 minutes, the pre-test will take approximately 160 minutes, the pos-test will take approximately 180 minutes, the first follow-up assessment takes 180 minutes and the second and third follow-up assessment will take approximately 110 minutes. For the participants in the fMRI study, the pre- and post MRI appointments will both take approximately 90 minutes. For participants randomised in the experimental group, the intervention consists of 20 sessions of 75 minutes. For participants randomised in the control group, 20 befriending sessions are organised. In the media material arts are sometimes associated with aggressive behavior. However, most research does not support this finding or shows opposite results. It is unlikely that kickboxing in itself increases aggressive behavior. Based on a recent feasibility study we don't expect any adverse events to happen for this reason and consider no such risks to be associated with participation.

## 1. INTRODUCTION AND RATIONALE

Contrary to what is generally thought, people with psychotic disorder are more likely to be a victim of a crime, than an offender (Brekke, Prindle, Bae, & Long, 2002; Dean et al., 2007). Prevalence rates vary between studies because of the differences in e.g. population samples, instruments, and time period covered. For example, between 16% (Walsh et al., 2003) to 33% (Bengtsson-Tops & Ehliasson, 2012) of people with psychotic disorders indicated they had been a victim of a violent crime in the preceding year. While looking at lifetime prevalence percentages range from 25% (Short, Thomas, Luebbers, Mullen, & Ogloff, 2013) to 78.8% (Dolan, O'Malley, & McGregor, 2013) depending on the definition of victimization and the time frame examined. In a recent Dutch study of Kamperman et al. (2014) 47% of the severe mentally ill outpatients reported that they had been a victim of a crime in the past year. Compared to the general population, people with severe mental illness reported fourteen times more incidents regarding personal crime such as sexual harassment or assault, threats of violence, and physical assault.

Victimization can have a major impact on the lives of already vulnerable patients, and ultimately entails high costs for society (Choe, Teplin, & Abram, 2008). The increasing deinstitutionalization of the mental health care system puts an increasing demand on the assertiveness of people with psychotic disorder, possibly enhancing the victimization risk in the future (Short et al., 2013). At this moment there is no evidence-based intervention that can decrease the victimization risk for people with psychotic disorder (Weeghel, Kamperman, Vries, Plooy, & Mulder, 2009), while both patients and caregivers indicate the need for one (Busschbach, Wiersma, & Slooff, 2012). Therefore, we are developing an intervention that aims to prevent victimization.

Before the development of the intervention we contemplated the underlying processes. Research has revealed several factors to be associated with victimization in patients with psychotic disorder. For example, alcohol and drug use (Chapple et al., 2004), homelessness (Walsh et al., 2003), perpetration (Honkonen, Henriksson, Koivisto, Stengård, & Salokangas, 2004), lack of meaningful daily activity (Fitzgerald et al., 2005), comorbid personality disorder (Dean et al., 2007), severe symptoms (Brekke, Prindle, Bae, & Long, 2001), and positive symptoms are all associated with an increased risk of victimization (Cohen, Palekar, Barker, & Ramirez, 2012). Not all of these factors can be readily addressed in one psychomotor intervention. For this reason, we developed a model in which we selected some of the important risk factors that may lead to victimization and are amendable to change (see Figure 1).

The first risk factor we would like to address is social cognition (DePrince, 2005). Compared to the general population people with a psychotic disorders have more difficulty with recognizing facial expressions (Evangeli & Broks, 2000), body language (Phillips & Seidman, 2008), and

emotional prosody (Hoekert, Kahn, Pijnenborg, & Aleman, 2007). This may complicate the judgment of risky social situations. For instance, they may not see it coming when one of their friends is going to be aggressive.

[figure not shown]

Figure 1: Victimization model

The second factor is insight, according to Ekinici & Ekinici (2013) poor insight is one of the pathways to aggression in schizophrenia. Poor insight in own psychotic symptoms may result in aggressive behavior creating dangerous situations for others as well as for themselves (Hiday, Swartz, Swanson, Borum, & Wagner, 1999). In accordance, problems in aggression regulation are associated with violent behavior in patients with a psychotic disorder (Witt, van Dorn, & Fazel, 2013). For this reason aggression regulation is the third risk factor that will be addressed. By addressing these three risk factors the intervention may improve social behavior and decrease victimization risk.

Another factor that may play a role in victimization is self-stigma. There is a lot of prejudice beliefs about mental illnesses. Most patients are aware of these and believe some of them (Brohan, Elgie, Sartorius, & Thornicroft, 2010). Victimization can increase self-stigma (Horselsenberg, Pijnenborg & [name], submitted), resulting in low self-efficacy (Kleim et al., 2008), low self-esteem and reduced empowerment (Livingston & Boyd, 2010). Consequently, people may not stand up for themselves in social situations and are therefore more prone to become a victim (Egan & Perry, 1998), which in turn increases self-stigmatic ideas and feelings of helplessness making this a self-enforcing process. Victimization not only affects self-stigma but also reinforce the other risk factors mentioned in the victimization model, increasing the chance of revictimization.

In addition, the traumatic experience of being a victim could lead to a strong physiological response to external stressors (Peri, Ben-Shakhar, Orr, & Shalev, 2000) and a compromised

inhibitory control (Falconer et al., 2008). In accordance, people who suffer from trauma or stress could react more aggressive in social situations (Makin-Byrd, Bonn-Miller, Drescher, & Timko, 2012; Volavka & Citrome, 2011). This aggressive response may elicit conflicts, again putting people at risk for victimization. Ultimately, people can become trapped in a downward spiral and need help to emerge from this vicious victimization cycle.

To address these specific risk factors we developed a psychomotor assertiveness training with elements of kickboxing. We chose a psychomotor approach because the results of body and movement oriented therapies look promising for people with a psychotic disorder (Röhricht, 2009; Röhricht, Papadopoulos, Suzuki, & Priebe, 2009). More research is warranted but review studies of Holley et al. (2011) and Malchow et al. (2013) show that physical exercise therapy, varying from swimming, football to cardiovascular exercise could have a positive effect on self-efficacy, self-esteem, social interaction skills, and positive and negative symptoms. These effects show an overlap with the risk factors in the victimization model and could help to decrease victimization risk. The same is true for assertiveness training. Assertiveness training can improve self-esteem, perceived control, assertiveness, and self-efficacy (Brecklin, 2008). Improving these factors may have a positive effect on social behavior and decrease victimization risk (see Figure 1 victimization model).

The intervention includes martial arts techniques. Several studies suggest that martial arts could have a positive effect on e.g. aggression regulation and social interaction (Elling, Wisse, & Berk, 2010; Lakes & Hoyt, 2004; Twemlow et al., 2008; Zivin et al., 2001). Our main technique is kickboxing since this is a sport that integrates both a strong focus on regulatory techniques with physical exercises. Furthermore, basic kickboxing techniques are achievable for everyone regardless of someone's physical condition. The active exercises in kickboxing may contribute to a pleasurable sportive experience in the sessions and give enough opportunities to address the risk factors. In the media, martial arts are sometimes associated with aggressive behavior. Most research does not support this finding or shows opposite results (Elling et al., 2010; Vertonghen & Theeboom, 2010). Some studies show that children or adolescents who practice fighting sports are more aggressive, compared to people who practice other types of sport. However several confounders play a role here as these studies are cross-sectional: more aggressive youths choose for example kickboxing because of its hard reputation (Elling et al., 2010; Lamarre & Nosanchuk, 1999; Vertonghen & Theeboom, 2012). Other factors that may play a role in these aggressive outcomes are a negative 'macho' environment at the gym (Eddehbia & Van der Putte, 2009; Endresen & Olweus, 2005), and competitive and performance oriented guidance (Nosanchuk & MacNeil, 1989). Kickboxing in a non-competitive non-commercial setting has been shown to have positive psychological effects and not enhance everyday aggression (Elling et al., 2010). In conclusion, it is unlikely that kickboxing in itself increases aggressive behavior.

## 2. OBJECTIVES

In preparation of the proposed multicentre randomized controlled trial (RCT), the psychomotor assertiveness training was tested in a feasibility study (n=23, dossier number NL49520.042.14, ABR number 49520). Subsequently, the intervention protocol has been evaluated and improved. The proposed study aims to investigate the effects of a psychomotor assertiveness training by means of a multicentre randomized controlled trial (RCT). Effects will be examined at the behavioural level by means of questionnaires and interviews, and at the cerebral level with an fMRI task. The effect on actual victimisation will be investigated as a long term outcome, because the prevalence of incidents is low thus we expect that effects of the intervention will only be visible after a longer period of time. Short term effects on risk factors of victimization (e.g. social cognition, self-stigma, assertiveness, self-esteem, aggression regulation, social behaviour) will be examined, since these are direct targets of the intervention. We expect that the risk factors will mediate the effect between the training and victimization.

## 3. STUDY DESIGN

The proposed study is an RCT with a pretest, two posttests and two follow-up assessments. A flowchart of the design is presented in Figure 2. For a detailed description of the recruitment and consent procedure see 7.5 and for the study procedure see 5.3.

[figure not shown]

Figure 2: Flow chart of study design

## STUDY POPULATION

## **4. STUDY POPULATION**

### **4.1 Population (base)**

Participants are individuals with a diagnosis in the psychotic spectrum and will be recruited from GGZ Drenthe, GGZ Friesland, GGZ Centraal, Dimence, Arkin, Lentis and UCP. Both in- and outpatients can be included in the study.

### **4.2 Inclusion criteria**

In order to be eligible to participate in this study, a participant must meet all of the following criteria:

- A diagnosis in the psychotic spectrum, according to DSM-IV-TR criteria, verified by MiniScan;
- Being able to give informed consent;
- 18 years or older;

### **4.3 Exclusion criteria**

A potential participant who meets any of the following criteria will be excluded from participation in this study:

- Florid psychosis (mean positive symptoms > 5 measured by PANSS);
- Substance dependence (not substance abuse) of alcohol, marijuana, opiates, stimulants and cocaine, verified by Miniscan.
- Estimated IQ < 70, onsite therapist decides if the patients intelligence is sufficient for participation.
- Co-morbid neurological disorder, verified by onsite therapist.
- Co-morbid personality disorder, verified by onsite therapist.
- Pregnancy.
- Current participation in martial arts classes.

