#### Module 5 Repeat and combine

In the fifth module exercises and topics from previous modules are combined and repeated when necessary. Furthermore, participants are stimulated to continue martial arts in a regular

sporting gym. A guest trainer from a local fighting school is invited to give a lesson of 30 minutes, making the step to a regular school more accessible for the participants.

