### **8.5 Recruitment and consent**

Chapter 2 shows a flow chart of the study design and main procedures. First the onsite therapist will answer seven screening questions about their patients (see appendix F1). When the answers are in accordance with the selection criteria (see 3.2 and 3.3 for inclusion and exclusion criteria) the patient will receive a phone call from his/her psychomotor therapist or another caregiver from his/her mental health institution. The assessor will inform the patients about the study and ask them if they are interested in participation and if they would like to receive an information letter about the study (see appendix E2). The assessor will send this letter by mail or email depending on what the patient prefers. Patients have two weeks to consider their participation. After two weeks, patients are contacted again to ask whether they decided to participate in the study.

During the first phone call all patients are also invited for a one hour information meeting. In this meeting patients will get more detailed information about the study procedures and the intervention and get acquainted with the trainers. The patients are invited to bring family and/or friends to this meeting in order to support and motivate patients for participation. Also, their questions about the intervention can be answered. All the involved mental health care professionals will also receive an invitation for the meeting (see appendix E3). When patients have second thoughts after the meeting they are free to refrain. After the information meeting the assessor will call all the interested patients to make an appointment for the selection assessment. The assessor will tell them again about the study procedures, randomization and intervention in case something was not clear during the meeting or someone did not attend the meeting. In addition, the patients are told that the intervention is in an experimental phase, and that no guarantees can be given regarding decreasing victimization risk. The selection assessment will start two to six weeks after the information meeting. On the day of the assessment the assessor first asks the patients to read and sign an informed consent form (see appendix E1).

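### Section 4.3 bars current martial arts classes but not earlier receipt of this training, so feasibility-study participants could be enrolled, unrecorded, in either arm (minor)

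*Protocol*

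**What the plan says.** The only criterion in Section 4.3 of the protocol that touches on prior exposure is "Current participation in martial arts classes". The rest of that list covers florid psychosis, substance dependence, estimated IQ, neurological and personality disorder, and pregnancy. Section 4.2 asks for "A diagnosis in the psychotic spectrum, according to DSM-IV-TR criteria, verified by MiniScan", the ability to consent, and age 18 or over. It sets no condition on earlier training.

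Section 2 states that "the psychomotor assertiveness training was tested in a feasibility study (n=23", under its own dossier number). It then says: "Subsequently, the intervention protocol has been evaluated and improved". Section 5.1 adds that some exercises were adapted after feedback.

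On recruitment, Section 4.1 says participants "will be recruited from GGZ Drenthe, GGZ Friesland, GGZ Centraal, Dimence, Arkin, Lentis and UCP". The sites of the feasibility study are not given. Section 8.5 describes the first screen: "First the onsite therapist will answer seven screening questions about their patients (see appendix F1"), with the answers compared against the selection criteria.

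Module 5 in Section 5.1.1 says that "participants are stimulated to continue martial arts in a regular" gym after the training.

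**The concern.** A criterion on martial arts exposure was evidently thought necessary, yet it leaves out the exposure closest to the trial: previous receipt of the investigational training itself. Among former trainees, the rule removes those who went on to a gym and still attend. It admits those who stopped.

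A former trainee allocated to befriending would be a control patient who has already had a version of the experimental treatment. One allocated to training would be having it a second time. In both cases the pre-test might not be an untreated baseline. If the earlier training had any lasting effect, such patients would add little to the contrast between arms, and the estimated difference would move toward zero on victimization and on the mediators. Because the protocol does not plan to record prior exposure, these patients could not later be identified, adjusted for or set aside in a sensitivity analysis.

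**Working it through.** **Step 1: is there a second safeguard in the text?** Four places could provide one.

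- Covariates (Section 6.1.4): substance use, gender, family contact, age, medication and safety of the residential area. Prior training is not listed.
- Randomisation (Section 6.2): site, gender and fMRI participation. Prior training is not a factor.
- Instrument schedule (Section 6.3, Table 5): no item records earlier participation.
- Screening (Section 8.5): the seven questions are in appendix F1, which is not part of the text. They are described as serving the criteria in 4.2 and 4.3, which are silent on this.

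As written, a feasibility participant not now in classes is eligible and would not be identified as such.

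**Step 2: the plan's own figure.** Inputs from the sample size section: effect 0.50, two-sided alpha 0.05, power 0.80, drop-out 25%, 60 per group.

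- n per arm = 2 × (1.960 + 0.842)² / 0.50² = 63 (64 with the t distribution).
- Allowing for drop-out: 63 / 0.75 = 84 (64 / 0.75 gives 86).

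The stated 60 is not reproduced from these inputs. It would follow from a baseline-adjusted analysis with a correlation of about 0.53 to 0.54, which the protocol does not state. That is a separate matter. It is used here only to fix the starting power: 60 × 0.75 = 45 completers per arm, and power = Φ(0.50 × √(45/2) − 1.960) = Φ(2.372 − 1.960) = 0.66.

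**Step 3: attenuation.** Let k former trainees enrol and split evenly between arms, as randomisation would give on average. Assume they carry no between-arm difference (full persistence), drop out at the same rate as others, and leave the standard deviation unchanged. Then

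- share per arm f = (k/2)/60
- attenuated effect d = 0.50 × (1 − f)
- power = Φ(d × √(n/2) − 1.960), with n completers per arm.

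For k = 23: f = 11.5/60 = 0.192; d = 0.50 × 0.808 = 0.404; power at 45 = Φ(0.404 × 4.743 − 1.960) = Φ(−0.043) = 0.48.

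| Former trainees enrolled | Share per arm | d | Power, 45 per arm | Power, 60 per arm |
|---|---|---|---|---|
| 0 | 0% | 0.50 | 0.66 | 0.78 |
| 2 | 1.7% | 0.49 | 0.64 | 0.77 |
| 5 | 4.2% | 0.48 | 0.62 | 0.75 |
| 12 | 10.0% | 0.45 | 0.57 | 0.69 |
| 23 | 19.2% | 0.40 | 0.48 | 0.60 |

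If only half the effect persists and all 23 enrol, the effective share is 0.5 × 0.192 = 0.096. Then d = 0.45, with power 0.57 at 45 per arm and 0.70 at 60.

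Two to five re-enrolments cost between 0.660 − 0.645 = 0.015 and 0.660 − 0.623 = 0.037 in power at 45 per arm, that is about 2 to 4 percentage points.

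**The case against.** The strongest reply is that harm needs three things, none of which the protocol shows: feasibility participants in the recruitment pool, actual re-enrolment, and an effect that lasts. The feasibility sites are not named. The opening of Section 5.1 was not in the text reviewed, and appendix F1 may contain a relevant question. Efficacy is what the trial is meant to establish, so full persistence is an extreme assumption. Recruitment starts with a therapist's screen and a call, not self-referral, and anyone who followed the Module 5 advice and still attends is already excluded. All of this stands, and it limits the size of the problem. It does not change what the criteria permit.

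A reader might infer stronger versions of the point, which the documents do not support.

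- *That 23 patients have already had this same treatment.* Section 2 gives n=23 for the study. It does not say that all 23 received or completed the training, and the intervention was revised afterwards. The supported wording is up to 23 people and an earlier version.
- *That the control arm in particular is contaminated.* The exposure precedes randomisation. It is a baseline characteristic spread over both arms by chance, so it favours neither arm systematically. The expected result is dilution.
- *That someone who recently left an ordinary martial arts class should also be barred.* Such classes are not the five-module intervention, and excluding only current attendance is a defensible choice. A look-back period would be a preference, not a correction.

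**Conclusion.** The gap is real but minor. Following Section 4.3 as written would admit previously trained patients to either arm without any record of it, and the only expected statistical consequence is attenuation toward no difference. The effect stays at 0.50 if none re-enrol and is about 0.48 with five. It falls to 0.40 if all 23 re-enrol, split evenly and keep the full effect, which is an upper bound. Corresponding power at 45 completers per arm is about 0.66, 0.62 and 0.48. Site overlap, re-enrolment and persistence are all assumptions, and the true cost may be zero. The correction is warranted because it is so cheap, not because damage has been shown.

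**What to change.** Add one criterion to Section 4.3: *Previous participation in the psychomotor assertiveness training, including the feasibility study.* Check it with one question to the patient at the selection assessment. The existing criterion on current classes can stay as it is.

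The check should not depend on a list from the feasibility study, since the protocol does not say that the trial team holds one. The cost is one line, one question and the loss of at most 23 candidates. If the sponsor prefers to keep former participants eligible, the protocol should say so and record prior exposure at baseline, so that it can be described and examined in a sensitivity analysis.

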### **4.4 Additional exclusion criteria for the fMRI-part**

All participants will fill out a questionnaire covering safety aspects and exclusion criteria of research in a 3 Tesla magnetic field and MRI environment. Exclusion criteria are:

- MR incompatible implants in the body (such as ear prosthesis or other metal implants)
- Any risk of having metal particles in the eye, due to manual work without proper eye protections
- Tattoos containing red pigments
- (Suspected) pregnancy
- Claustrophobia

- Refusal to be informed (by notifying the patients physician) of structural brain abnormalities that could be detected during the experiment

#### **4.1 Sample size calculation**

Sample size was calculated using the computerprogram SPSS Sample Power. In order to find a medium effect size (0.50) with two-sided  $\alpha=0.05$ , power=0.80 and taking 25% drop-out into account, 60 participants per group are needed. This means a total sample size of 120 participants.

Sample size in fMRI studies is usually not determined by power analyses, but by experiences with similar protocols. Exact power calculations are difficult because of the complex 'mass univariate' nature of brain imaging data as well as the difficulty to estimate effect sizes in different regions of interest beforehand. Previous studies suggest that in general, 20 participants are necessary per group to achieve sufficient power and acceptable reliability (Monti, 2011; Thirion et al., 2007). Therefore, in the fMRI-part of the proposed study, 22 participants will be included per group.

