**Main study parameters/endpoints**

Primary study outcome is the long term effect of the psychomotor assertiveness training with elements of kickboxing on victimization, as measured by two questionnaires which examine whether an individual has been victim of a crime. We expect that this effect will be mediated by risk factors of victimization (e.g. social cognition, internal stigma, assertiveness, self-esteem, aggression regulation, social behaviour), as measured by both behavioural and cognitive measures such as interviews, questionnaires and a neuropsychological test, and cerebral measures such as fMRI paradigms. Secondary long term outcome measures are quality of life, recovery, social participation, negative symptoms and coping with trauma.

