### **Integrale Veiligheidsmonitor**

The Integrale Veiligheidsmonitor (IVM) is a Dutch crime and victimization survey that resembles the international crime victimization survey (CBS, 2009). We will use the victimization subscale (Victrom: Kamperman et al., 2014) and the subscales about safety perception in general and in one's neighborhood. Participants will complete the IVM pre- and post- treatment as well as during both follow up assessments, since we are particularly interested in victimization in the long term. The time-frame in the questions will be adapted, in order to investigate victimization between two subsequent assessment points. At baseline, the time-frame consists of the past five years. At both post assessments, victimization of past six months will be examined. At follow-up victimization of the past year will be assessed.

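### Section 4.1 states 80% power at an effect of 0.50 without naming an endpoint, and that power does not follow from its own inputs or carry over to victimization, the primary outcome

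*Protocol*

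**What the plan says.** Protocol section 4.1 (Sample size calculation) gives the only power statement for the main comparison. It starts "In order to find a medium effect size (0.50) with two-sided" testing at 0.05, continues "power=0.80 and taking 25% drop-out into account, 60 participants per group are needed", and concludes "This means a total sample size of 120 participants". It attaches no outcome, scale, standard deviation, event rate or time point to the 0.50.

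The primary outcome is the long-term effect on victimization, "as measured by two questionnaires which examine whether an individual has been victim of a crime" (Summary, Main study parameters/endpoints). The instruments are the IVM and the CTS2 (6.1.2, Table 4). On the IVM time frame the Protocol says "At follow-up victimization of the past year will be assessed". The CTS2 items are rated from 1 to 8 by frequency. Section 8.2 analyses victimization by repeated measures ANOVA, and section 8.3 refers to IVM results as scores.

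On frequency, section 2 places victimization in the long term "because the prevalence of incidents is low thus we expect that effects of the intervention will only be visible after a longer period of time". Section 1 cites one-year rates of 16% and 33% for violent crime, and a Dutch survey in which "47% of the severe mentally ill outpatients reported that they had been a victim of a crime in the past year".

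**The concern.** Calling 0.50 a medium effect is a convention for continuous scales. It suits the risk-factor questionnaires, but nothing in the Protocol links it to victimization. On an outcome described as infrequent, half a standard deviation can be a very large change, so a power figure quoted for 0.50 may say little about the primary question. Separately, 60 per group does not look like enough for 0.50 once a quarter of participants are lost.

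What is at stake is how a non-significant primary result is read. Set against a stated 80% power for a medium effect, it would be taken as fair evidence that the training does not prevent victimization, when a substantial reduction could well have been missed.

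**Working it through.** **Step 1. The printed figure on its own inputs.** Inputs from section 4.1: d = 0.50, two-sided 0.05, power 0.80, drop-out 25%, 60 per group.

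- Evaluable number needed per group: n = 2(1.96 + 0.8416)² / 0.50² = 62.8, so 63. The t-test needs 64.
- Inflated for drop-out: 63 / 0.75 = 84, or 64 / 0.75 = 85.3, so 86. The printed 60 is not reproduced.
- Evaluable number left by 60 per group: 60 × 0.75 = 45.
- Power at d = 0.50 (t-test): 65% with 45 per group and 78% with all 60.
- Effect detectable with 80% power (t-test): d = 0.60 with 45 and d = 0.52 with 60.

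Two variants also miss 60. Multiplying by 1.25 instead of dividing by 0.75 gives 79 to 80. One-sided testing gives 67 to 68.

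**Step 2. What 0.50 means for victimization, if it is a yes/no outcome.** This reading is an assumption. For control rate p, solve for q in (p − q) / √{[p(1 − p) + q(1 − q)] / 2} = 0.50, with p taken from section 1.

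| One-year control rate p | Rate q at d = 0.50 | Relative reduction |
|---|---|---|
| 47% (any crime) | 23.8% | 49% |
| 33% (violent crime) | 12.6% | 62% |
| 16% (violent crime) | 2.1% | 87% |

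The arcsine effect size gives nearly the same range (50% to 84%). A log-odds conversion, which supposes a latent logistic scale, gives 44% to 55%.

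**Step 3. Power for a halving in one one-year comparison.** Method: exact enumeration over two binomials with equal arms, rejecting by the two-sided 5% t-test on 0/1 data.

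| Control rate | Halved rate | Implied d | Power, 45 per group | Power, 60 per group |
|---|---|---|---|---|
| 47% | 23.5% | 0.51 | 66% | 77% |
| 33% | 16.5% | 0.39 | 44% | 57% |
| 16% | 8% | 0.25 | 23% | 27% |

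**Step 4. Reduction detectable with 80% power, same method.**

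| Control rate | 45 per group: falls to (points) | 60 per group: falls to (points) |
|---|---|---|
| 47% | 19.8% (27) | 22.8% (24) |
| 33% | 9.6% (23) | 12.2% (21) |
| 16% | 1.4% (15) | 2.3% (14) |

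**The case against.** **The primary measure is not fixed as yes/no.** This stands. The CTS2 frequency items, the reference to IVM scores and the planned ANOVA all allow a score, for which 0.50 SD has no fixed percentage meaning. A reader might infer that 0.50 simply means removing 49% to 87% of victimization. The Protocol supports that only conditionally, and the upper end also depends on the conversion used. Step 1 does not depend on this reading.

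**The low rates are poorly matched.** This stands too. The 16% and 33% are violent crime only, while the IVM is a general crime survey and the CTS2 adds subtler events, so both rates are probably below what these instruments capture. The 47% is the closest match, although it comes from outpatients with severe mental illness more broadly. At 47% a halving is almost exactly d = 0.50, so the shortfall there is the drop-out arithmetic of Step 1. At lower rates the choice of 0.50 adds to it.

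**The plan is not a single-window test.** Correct. A reader might infer from Step 3 that the trial discards follow-up data. It does not: Table 5 schedules the IVM and CTS2 at every assessment from baseline on, and section 8.2 plans a repeated measures analysis. As an illustration, assume the average of three equally informative waves with between-wave correlation 0.3 to 0.7. Power for a halving at 45 per group would then be about 76% to 90% at 47%, 53% to 71% at 33%, and 26% to 36% at 16%. Likewise, an unstated baseline correlation of about 0.53 to 0.54 would bring the requirement in Step 1 down to 45. Section 4.1 claims neither gain and gives no correlation.

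**Drop-outs may still be assessed.** Section 6.5 invites withdrawn participants to later assessments, so the evaluable number may lie between 45 and 60. It would therefore be too strong to say that a halving would usually be missed at 33%: that holds with 45 per group (44%) but not with 60 (57%).

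**Pooling all follow-up windows into one primary contrast.** This may look like the natural remedy, but the Protocol does not support it as a correction. Its apparent gain rests on a constant risk for everyone, whereas sections 1 and 8.6 describe victimization as self-reinforcing.

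**Conclusion.** The power statement is wrong as written. On the inputs of section 4.1, the trial has about 65% power at d = 0.50 with the 45 per group left after drop-out, and 78% if nobody is lost. This rests only on a two-group comparison without covariate gain, which is all that section 4.1 describes.

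The 0.50 is also not tied to the primary outcome. On the yes/no reading, and in a single one-year comparison, 80% power for a halving is not reached at any of the cited rates with either 45 or 60 per group. The shortfall is modest at 47% and large at 16%. The repeated measures analysis could narrow the gap, and at 47% might close it, but the Protocol gives no basis for counting on that.

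**What to change.** Rewrite section 4.1 in three respects.

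1. State which outcome, scale and time point the 0.50 refers to.
2. Replace the 80% with the power that 45 to 60 evaluable per group give: about 65% to 78% at d = 0.50, with about d = 0.60 detectable at 80% power with 45. If a gain from repeated or baseline measurement is claimed, print the correlation assumed.
3. Print the reduction in victimization detectable with 80% power. On the yes/no reading, at 45 / 60 per group, this is about 27 / 24 percentage points from 47%, 23 / 21 from 33%, and 15 / 14 from 16%. State that a non-significant primary result is inconclusive for smaller reductions.

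The change costs one rewritten paragraph and needs no extra participants, visits or questionnaires. The downside is that the printed power becomes less favourable.
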